### Outcomes and participant timeline

Outcomes are reported in table 1 and were chosen collaboratively by children and young people with epilepsy and their parents, sleep and epilepsy experts^8 17^ in accordance with Core Outcome Measures in Effectiveness Trials guidelines.^30^ Psychometric properties and clinical relevance of outcomes are reported in online supplemental table 3. Each participant will be followed up for 6 months. The participant timeline and estimated time requirement are, respectively, shown in table 4 and online supplemental table 4.

**Table 4 T4:** CASTLE Sleep-E participant timeline and order of outcome completion

	T–4 weeks* Consent and baseline	T0† Randomisation	T+3 months Follow-up visit	T+6 months Follow-up visit
Visit no	1	2	3	4
Informed consent/assent	X			
Review of medical history and EEG results	X			
Eligibility confirmation	X	X		
COVID-19 screener	X		X	
Review of seizure occurrence		X	X	X
Hospital admissions		X	X	X
Demographics	X			
School absences		X	X	X
Check contact details for accuracy		X	X	X
Children’s Sleep Habit Questionnaire^33^	X		X	X
SleepSuite^34^ (iPad)	X		X	
WHO–Five Well-Being Index^50^	X			X
Health-Related Quality Of Life Measure for Children with Epilepsy^55^	X			X
Strengths and Difficulties Questionnaire^51^	X		X	X
CHU-9D/CHU-9D proxy^39^	X		X	X
EQ-5D-Y/EQ-5D-Y proxy^40^	X		X	X
EQ-5D-5L^54^	X		X	X
Parenting Self-Agency Measure^52^	X		X	X
Insomnia Severity Index^43^	X		X	X
Hospital Anxiety and Depression Scale^49^	X		X	X
Resource Use Questionnaire	X		X	X
Knowledge about Sleep in Childhood	X		X	
Randomisation Standard care (SC) or (SC+COSI)^16^		X		
Intervention arm only: COSI^16^				
Actigraphy and sleep diary^53^ (14 days)	X		X	
Confirm continuing trial participation			X	X
Assessment of serious adverse events			X	X
Completion of follow-up Case Report Form			X	X
Review of concomitant medications		X	X	X
Qualitative interview‡			X	X

*Up to 4 weeks flexibility between consent and randomisation to allow delivery of actigraph and iPad.

†Randomisation may be performed once 2 weeks of actigraphy and the minimum dataset are complete.

‡Optional trial component: consenting participants are interviewed within 3 weeks of follow-up visits 3 and 4.

CASTLE, Changing Agendas on Sleep, Treatment and Learning in Epilepsy; CHU-9D, Child Health Utility Index 9D; COSI, CASTLE Online Sleep Intervention; EEG, electroencephalogram.

### Sample size

The target sample size (110 children with RE, 55 per trial arm) was calculated based on achieving 90% power to detect the minimal clinically important difference (MCID) in the primary clinical outcome (Children’s Sleep Habits Questionnaire (CSHQ)) at 3 months after randomisation, accounting for 10% expected attrition (non-parametric test with two-sided 5% significance level). MCID was defined based on an individual-focused anchor-based method,^31^ that is, ‘the smallest difference in outcome that patients perceive as beneficial and which mandates a change in patient management’.^32^ The MCID value was based on the estimated reduction in total CSHQ score required for children with epilepsy (M=48.25, SD=8.91)^7^ to fall at or below the diagnostic cut-off score of 41 for sleep disorders in paediatric populations.^33^

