## Methods and analyses

### Trial design

CASTLE Sleep-E is a UK-based, multicentre, open-label, active concurrent control, randomised (1:1), parallel-group, pragmatic superiority trial (overall trial start date: 14 May 2018, first trial site opened: 12 May 2022, first recruitment: 30 August 2022, planned trial end date: 31 July 2023). Compared are clinical and cost-effectiveness of SC alone and SC augmented with a novel, tailored, parent-led COSI (SC+COSI) in reducing sleep problems in children (5–<13 years) with RE at 3 and 6 months after randomisation. Parents and children (≥7 years) can opt into qualitative interviews and activities to share their experiences and perceptions within 3 weeks of completion of other data collection at 3 and 6 months after randomisation.

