### Recruitment, stopping guidelines and interim analyses

An Independent Data and Safety Monitoring Committee will monitor recruitment and make recommendations to the Trial Steering Committee (TSC) concerning trial continuation, adjustments of recruitment methods and follow-up optimisation (see online supplemental table 2). A traffic light approach will determine trial continuation: (1) green: continue if at least 30 trial sites have opened and 22 participants have been randomised by end of month 6; (2) amber: implement additional recruitment strategies if 15–21 participants have been randomised by end of month 6; (3) red: if recruitment is <15 participants by end of month 6, then stopping the trial early will be discussed with the TSC. Formal interim analyses of the accumulating data will not be performed.

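### With a Mann-Whitney-type test the printed inputs need about 76 to 86 children, not 110, so the effect carrying 90% power is misdescribed; the recruitment dates and go rule also need reconciling

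*Protocol article*

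**What the plan says.** Protocol article, Sample size: the target is "110 children with RE, 55 per trial arm". It "was calculated based on achieving 90% power to detect the minimal clinically important difference (MCID) in the primary clinical outcome" (CSHQ total score at 3 months), with 10% expected attrition and a "non-parametric test with two-sided 5% significance level". The test is not named. The MCID is not given in points. It is described as based on the reduction that children with epilepsy (mean 48.25, SD 8.91) would need to "fall at or below the diagnostic cut-off score of 41".

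Protocol article, Trial design: "first recruitment: 30 August 2022, planned trial end date: 31 July 2023"; the first site opened on 12 May 2022. The Outcomes and participant timeline section gives every participant 6 months of follow-up.

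Protocol article, Recruitment, stopping guidelines and interim analyses: green is "continue if at least 30 trial sites have opened and 22 participants have been randomised by end of month 6". Amber is 15 to 21 randomised and red is fewer than 15, both by the end of month 6. The section does not say from which date the months are counted.

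**The concern.** The section prints the inputs and the result, so they can be checked against each other. With the usual non-parametric test for two groups they do not agree. Either the MCID behind 110 was smaller than the cut-off rationale implies, or the SD was larger, or the test was an unusual one, or the power is higher than stated.

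What is at stake is interpretation. The result will be read against the MCID. If the trial was sized for about 6 points, the link between the MCID and reaching the diagnostic cut-off is lost. If it was sized for 7.25 points, the stated 90% is too low and more children are being asked for than the stated aim requires.

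The recruitment rule raises a smaller question of the same kind: whether target, follow-up, end date and go threshold describe one feasible timetable.

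**Working it through.** **Inputs (Sample size section).** Mean 48.25, cut-off 41, SD 8.91, power 90%, two-sided 5%, attrition 10%, 55 per arm. Derived: MCID = 48.25 − 41 = 7.25 points; standardised, 7.25/8.91 = 0.814. I assume that the SD used was the printed 8.91.

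**Attempt to reproduce 110.** For two means, n per arm = 2(1.960 + 1.2816)² / 0.814² = 31.7. For a rank test, divide by its asymptotic relative efficiency (ARE), round up, then divide by 0.9 for attrition:

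| Method | Evaluable per arm | Randomised per arm | Total |
|---|---|---|---|
| Normal approximation, no rank correction | 31.7 → 32 | 36 | 72 |
| Mann-Whitney, normal data (ARE 0.955) | 33.2 → 34 | 38 | 76 |
| Mann-Whitney, worst case (ARE 0.864) | 36.7 → 37 | 42 | 84 |
| Noether's formula | 74.05 in total → 38 | 43 | 86 |

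Noether's formula uses P(X<Y) = Φ(0.814/√2) = 0.7175, so N = (1.960 + 1.2816)² / [3 × (0.2175)²] = 74.05. Starting from the t-based 33 per arm moves the Mann-Whitney totals up by at most a few, to 78 and 88. None gives 110. A fall to strictly below 41 would be larger than 7.25 and would need still fewer children.

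**What does give 110.**
- A difference of 6 points with SD 8.91: 31.74 × (7.25/6)² = 46.3; /0.955 = 48.5 → 49; 49/0.9 → 55 per arm, exactly 110. A 6-point fall ends at 48.25 − 6 = 42.25.
- A difference of 7.25 points with an SD of about 10.3 to 10.9 (ARE 0.864 to 0.955).
- A median-type test (ARE 2/π = 0.637) with the printed inputs: 31.74/0.637 = 49.9 → 50; 50 × 1.1 = 55 per arm (110), or 50/0.9 → 56 per arm (112).

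**Power at 110.** 55 × 0.9 = 49.5, so about 49 evaluable per arm. Power = Φ(0.814 × √(49 × ARE/2) − 1.960), which is 0.976 at ARE 0.955 and 0.963 at ARE 0.864. Simulated Mann-Whitney power on normal data was 0.972 at 49 per arm, against 0.895 at 34 and 0.923 at 38. The difference with 90% power at 49.5 per arm is 5.94 points (ARE 0.955) to 6.25 points (ARE 0.864).

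**Timetable.** With 6 months of follow-up and an end on 31 July 2023, the last fully followed randomisation is about 31 January 2023. From 30 August 2022 that is 154 days, or 5.06 months; 110/5.06 = 21.7 per month. For the 3-month primary outcome alone the last date is about 30 April 2023, giving 7.98 months and 110/7.98 = 13.8 per month.

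Month 6 ends on:
- about 28 February 2023 if counted from first recruitment, which is after 31 January 2023;
- 12 November 2022 if counted from first site opening. A trial at exactly 22 would then need 110 − 22 = 88 more in 2.63 months, or 33.5 per month, for full follow-up.

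**Categories.** Green needs both 22 or more children and 30 or more sites. Amber stops at 21 children and red is below 15. So 22 or more children with fewer than 30 open sites is unassigned.

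**The case against.** The strongest reply is that the article never names the test and never prints the MCID. It says only that the value was based on the reduction to the cut-off, and a condensed article may leave both details to the full protocol. With a median-type test the printed inputs do reach 110 to 112 at 90% power. A reader might infer from the table above that 110 cannot come from these inputs at all; that goes too far. What stands against the reply is that nothing in the text points to a median-type test, and a Mann-Whitney-type test is the ordinary reading. The article also chose to print both inputs and result.

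The discrepancy also runs in the safe direction. That is right, and it limits the point to description. Sizing on a simple unadjusted test when the primary analysis is a baseline-adjusted mixed model is common and usually conservative, so I do not count it as an error.

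On recruitment, 22 is a floor for continuing while up to 40 sites open. It is not a planned rate, and the monitoring committee can recommend changes to recruitment methods. Three stronger readings are therefore unsupported:
- That the target cannot be reached: later accrual may be faster than the floor.
- That the primary analysis would end badly underpowered: this comes from cutting accrual at the 6-month follow-up date, whereas the primary outcome is at 3 months.
- That 110 is too large a share of the 542 new UK cases a year: nothing shown limits entry to new diagnoses.

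**Conclusion.** The sample-size point holds. On the printed inputs, with 7.25 points as the derived MCID, 8.91 as the SD and a Mann-Whitney-type test, 90% power needs about 76 to 86 children. At 110, power for 7.25 points is about 97%, and the difference with 90% power is about 6 points, which does not bring the mean to the cut-off. That 6 points gives exactly 110 suggests a different MCID was used, but does not prove it. This is not an underpowered trial and 110 need not change; the effect that the trial was sized for is misdescribed.

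The recruitment point is secondary and is one of consistency. The dates allow about 5 months of accrual with full follow-up, or about 22 children per month for 110, while green asks for 22 in total by a month 6 with no origin. On one reading that review falls after the last fully followed randomisation. One combination of children and sites has no category. These passages must be reconciled, but they do not show that the trial will miss its target.

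**What to change.** In the Sample size section, state the MCID in points, the SD and the test that gave 110. Then do one of the following:
- keep the cut-off rationale and restate power at 110 as about 97% for 7.25 points; or
- state that 110 gives 90% power for about 6 points, and correct the rationale, since 6 points does not reach 41.

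If a median-type test was in fact used, naming it and the attrition calculation would resolve the mismatch.

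In the recruitment section, define month 1. Reconcile the planned end date, the 6-month follow-up, the target and the traffic-light counts, so that the review falls before recruitment must close. Assign 22 or more children with fewer than 30 open sites to a category.

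The cost is protocol wording and a review of committee thresholds and dates. No additional patients and no change to the primary analysis are needed.

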### Recruitment, stopping guidelines and interim analyses

An Independent Data and Safety Monitoring Committee will monitor recruitment and make recommendations to the Trial Steering Committee (TSC) concerning trial continuation, adjustments of recruitment methods and follow-up optimisation (see online supplemental table 2). A traffic light approach will determine trial continuation: (1) green: continue if at least 30 trial sites have opened and 22 participants have been randomised by end of month 6; (2) amber: implement additional recruitment strategies if 15–21 participants have been randomised by end of month 6; (3) red: if recruitment is <15 participants by end of month 6, then stopping the trial early will be discussed with the TSC. Formal interim analyses of the accumulating data will not be performed.

### Treatment allocation

Participants will be allocated with a 1:1 ratio to either SC or SC+COSI based on a computer-generated adaptive restricted randomisation procedure that minimises differences between trial arms in variables likely to affect outcomes. Minimisation algorithm details are not published to avoid subversion of allocation sequence concealment, but include seizure frequency, AED and sleep medication details. The allocation concealment mechanism is an online, central randomisation service implemented and maintained by the Liverpool Clinical Trial Centre (LCTC). The service will be accessed within 4 weeks of participant enrolment (once consent and eligibility confirmed, participant ID issued, baseline dataset completed) by trained, authorised staff at trial sites. Randomisation will trigger allocation emails to the trial manager at LCTC and to the relevant trial site as well as enable COSI access for participants allocated to the intervention arm. Trial sites will notify the participant’s general practitioner of the treatment allocation by letter (electronic or hard copy, depending on preference).

## Blinding

Only quantitative data analysts will be blinded (participant IDs do not reveal treatment allocation). All other stakeholders (participants, parents, healthcare providers, data collectors, qualitative researchers) will be aware of the allocated intervention. Emergency unblinding procedures are therefore unnecessary.

### Assent and consent

Potentially eligible children will be screened at trial centres by trained site staff. Screening outcome will be documented. Eligible children with interested parents will be invited to participate and provided with a Patient Information Sheet and Consent (PISC) Form electronically and/or hard copy (PISC, three versions: parent, child (5–6 and 7–12 years)). Sufficient time will be allowed for discussion of the trial and the decision to assent/consent to trial entry and the optional qualitative component. Assent (children aged 7–12 years) and consent (parents) may be given face-to-face or remotely and will be electronically captured in a secure Consent Database managed by LCTC. Reasons for declining participation will be asked, but it will be made clear that children and parents do not have to provide a reason.

### Data collection and management

Data collection will be carried out electronically except for Serious Adverse Events and Participant Transfer Forms (hard copy). At consent/assent, site staff will enter patient medical history (including EEG), eligibility confirmation, COVID-19 screening and demographics (see table 4) into eCRFs stored in a secure Data Management System managed by LCTC. Trial participation will be added to the patient’s medical records alongside their unique participant ID.

Consent and Contacts Databases are securely linked. The addition of a new participant will trigger email notifications to the parents containing access links to baseline assessments (see table 4) and the Sleep Team who will access the Contacts Database to arrange the delivery of an iPad preconfigured by LCTC (optionally fitted with prepaid SIMs), and two actigraphs with supporting documents. iPads (Generations 7–8, iOS V.15.2 or V.15.3) will be used to access the SleepSuite App (V.1.4),^34^ which assesses executive functions in child-friendly, interactive games (eg, popping virtual bubbles with smiling children’s faces). Access requires the participant ID and is only possible at prespecified trial time points (see table 4). Data are only stored on the iPad until the test session completion, then automatically uploaded to a cloud-based server, and then securely downloaded for analyses by authorised LCTC staff. Families lacking other means of internet access can use iPads fitted with prepaid SIMs to access other online trial materials (including email).

Actigraphs (Micro Motionlogger Watch and Watchware Software V.1.99.17.4, Ambulatory Monitoring, New York, USA) will be used to collect 14 days of objective sleep data from child and parent. Concurrent sleep diaries (hard copies) will be completed by the parent with or without child input. At the end of the baseline period, actigraphs will be returned to the Sleep Team via prepaid courier. The Sleep Team will download and securely store pseudo-anonymised (using participant IDs) actigraphy data for pre-processing (manual selection of sleep periods cross-checked against sleep diaries) per night at participant level. Summary variables (sleep latency, total sleep time and sleep efficiency) are then automatically calculated by actigraph software, manually collated and securely transferred electronically to LCTC for trial-level analyses by the trial statistician.

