### Fidelity, adherence, retention and acceptability

Fidelity (intervention delivery) will be monitored through e-analytics embedded in the COSI system (modules accessed and time spent per module). Strategies to improve completion of COSI training in case of non-access include: (1) an automated text reminder after 2 days; (2) an email reminder after 4 days; (3) a phone call from researchers who developed COSI (the Sleep Team) after 6 days. To improve adherence to the intervention, (1) all participants will receive a phone call from the Sleep Team 6 weeks after account creation; and (2) children will receive postcards with child-oriented activities (eg, maze) at three time points to welcome them to the trial (weeks 1–2), to stay in touch (weeks 4–5) and to thank them for participating (weeks 4–8 post-trial). To encourage completion of the intervention evaluation, participants will receive: (1) an automated text reminder after 3 days of non-completion, (2) and a phone call from the Sleep Team after 8 days of non-completion. Fidelity (intervention implementation, acceptability, perceived helpfulness) will be captured jointly by the COSI evaluation module and the qualitative trial component.

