### Data quality, security and trial oversight

Reliability, validity and clinical relevance of outcomes are reported in online supplemental table 3. Processes to promote quality and security of collected data include general local training of site staff and research teams (Good Clinical Practice), and trial-specific training in the use of electronic forms and databases by LCTC. LCTC will request to see evidence of appropriate training and experience of all trial staff. Staff will be signed off as appropriately qualified by the CI. Electronic data capture provides several in-built validity and security checks (eg, data type, range and missingness checks in eCRFs, SleepSuite use/access restrictions). Some electronic and all hard copy data will be repeat checked (eg, eligibility, contact details). Data processing requiring more subjective judgement will be performed by minimum of two trained researchers on at least a subset of data (ie, manually assisted selection of actigraphy sleep period; thematic and content analysis of qualitative data).

Data will be processed and stored in accordance with GDPR under the UK Data Protection Act 2018. Central data monitoring will be performed by LCTC which will raise and resolve queries with site and research teams within the online system. The University of Liverpool is registered with the Information Commissioners Office. LCTC will receive trial participants’ HES identifiers for secure transfer to the Health Economic Team, who will access, securely store and dispose of HES data in accordance with the Bangor University and NHS Digital Data Sharing Framework Contract.

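### Nothing in the article masks the Sleep Team, who developed COSI and phone COSI families, when they hand-select sleep periods in the 3-month actigraphy, a secondary outcome

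*Protocol article*

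**What the plan says.** All places are in the protocol article.

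- **Data collection and management.** "The Sleep Team will download and securely store pseudo-anonymised (using participant IDs) actigraphy data for pre-processing". That pre-processing is "manual selection of sleep periods cross-checked against sleep diaries", done night by night for each participant. The device software then calculates latency, total sleep time and efficiency, and the results are collated by hand and sent to LCTC for the trial statistician. The parent completes the paper diary, with or without the child. Device delivery is arranged by "the Sleep Team who will access the Contacts Database".
- **Fidelity, adherence, retention and acceptability.** When COSI has not been accessed there is "a phone call from researchers who developed COSI (the Sleep Team) after 6 days". Later, "all participants will receive a phone call from the Sleep Team 6 weeks after account creation". When the COSI evaluation is outstanding there is a text reminder, "and a phone call from the Sleep Team after 8 days of non-completion".
- **Blinding.** "Only quantitative data analysts will be blinded (participant IDs do not reveal treatment allocation"). Every other stakeholder group, data collectors included, is said to know the allocation.
- **Data quality, security and trial oversight.** "Data processing requiring more subjective judgement will be performed by minimum of two trained researchers on at least a subset of data". The selection of the actigraphy sleep period is named there as one example.
- **Tables 1 and 4.** Actigraphy is secondary outcome 11, recorded in child and parent at baseline and 3 months. Efficiency is defined as the percentage of the sleep period spent asleep. Randomisation may follow only once two weeks of baseline actigraphy are complete.

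**The concern.** The people who choose the scoring window built the intervention under test, and their phone duties bring them into contact with identifiable families in one arm. Where a boundary is unclear, knowledge of the arm could tilt the choice without any intent. The statistician's blinding comes too late to help, because the statistician receives summaries that already contain those choices.

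The actigraphy variables are the only device-based sleep measures in Table 1. CSHQ and the Insomnia Severity Index are questionnaires, and SleepSuite measures reaction time and executive function. The article calls the actigraphy data objective. A reader of the results will therefore give them weight as evidence that does not depend on an unblinded parent's report, and unmasked scoring by the developers weakens that claim.

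**Working it through.** **1. Can the scorers learn the arm?** The 6-day call is triggered by failure to access COSI, and only families allocated to SC+COSI receive access. The evaluation call concerns the COSI evaluation module, which is requested three months after access. Both calls therefore identify a family as being in the COSI arm. The 6-day call falls well before the 3-month recording and the evaluation call close to it. The 6-week call is ambiguous: it is said to go to all participants, yet it is timed from account creation, which suggests COSI accounts. The argument does not need it. Because the team also uses the Contacts Database, it has a route between a family and its trial record that an outside scorer would not have.

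**2. Does the Blinding section cover the scorers?** It blinds quantitative data analysts and nobody else. Data collection and management names the LCTC trial statistician as the person doing trial-level analyses. Counting the scorers as blinded analysts would conflict with the phone duties in step 1.

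**3. Do the other safeguards remove the problem?** Scoring by two researchers on a subset tests agreement, and two scorers who both know the arm can agree and share a tilt. The diary cross-check limits the scorer's discretion, but the diary is kept by a parent who knows the allocation. The summaries are computed by software, but on the period chosen by hand.

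**4. Which outcomes move?** The article gives no figures here, so the inputs are assumed: a selected period of 540 minutes with 460 minutes asleep, and latency counted from the start of the selected period. Removing *t* minutes of wake from the start lowers latency by *t* and gives efficiency 460/(540 − *t*):

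| *t* (min) | Efficiency | Change (percentage points) |
|---|---|---|
| 0 | 460/540 = 85.2% | – |
| 5 | 460/535 = 86.0% | +0.8 |
| 10 | 460/530 = 86.8% | +1.6 |
| 15 | 460/525 = 87.6% | +2.4 |

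With 480 minutes asleep the values run 88.9%, 89.7%, 90.6% and 91.4%. Total sleep time does not change in this example. It changes only if the boundary takes in or cuts off minutes scored as sleep.

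**5. What could a differential shift do to the error rate?** Take 49 per arm (55 × 0.9 = 49.5, rounded down), no true effect, and an average scoring difference *b* between arms. With SE = SD × √(2/49), the two-sided error is Φ(*b*/SE − 1.96) + Φ(−*b*/SE − 1.96). The article gives neither SD nor *b* for actigraphy, so both are assumed. For mean latency:

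| SD (min) | SE (min) | *b* = 2 min | *b* = 5 min |
|---|---|---|---|
| 15 | 3.03 | 10% | 38% |
| 20 | 4.04 | 8% | 24% |
| 30 | 6.06 | 6% | 13% |

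For example, with SD 15 and *b* = 5, *b*/SE = 1.65 and Φ(−0.31) + Φ(−3.61) = 0.38. These are simple two-sample figures. Adjusting for the baseline value, as Table 5 plans, may shrink the SE, but it does not remove a shift that arises at 3 months.

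**The case against.** The strongest reply is that unmasking is inferred. The recordings carry IDs that do not reveal the arm. The 6-day and evaluation calls reach only families who have not accessed or not completed, so some COSI families may never be phoned for those reasons. The Sleep Team is a group, and the article does not say that the same individuals phone and score. Duties may be divided in a scoring manual that an article would not reproduce. This part stands: a reader might infer that the scorers are known to hold the arm of every ID, and the documents do not say so. It does not remove the point, because the Blinding section restricts blinding to analysts. Masked scoring is thus excluded by what is written, and is not merely left to another document.

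Second, discretion is limited: the article elsewhere describes the selection as manually assisted, there is a diary cross-check, and a subset is scored twice. These features probably reduce the size of any tilt, but none of them masks the scorer.

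Third, a reader might infer that actigraphy is the trial's sole check on the CSHQ result. The article does not claim this. Its strengths and limitations list offers actigraphy, together with COSI e-analytics, against reliance on self-report when assessing implementation. The open-label design is also stated openly. That limits the consequence, and the point is worded accordingly.

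**Conclusion.** The point holds as a modest, correctable weakness. The article gives a subjective scoring step to the developers of the intervention, who also phone families in the COSI arm, and it restricts blinding to others. That scorers can link recordings to arm is a strong inference, not a stated fact.

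The scope is narrow. Baseline actigraphy is recorded before randomisation, so the exposure is the 3-month recording. The outcomes are secondary, chiefly latency and efficiency, with total sleep time affected only under a different kind of boundary error. It would be wrong to conclude that the primary CSHQ comparison is compromised, because this scoring does not enter it.

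The documents do not allow the size of any bias to be estimated. The error rates of 6% to 38% show how sensitive the comparison is to shifts of 2 to 5 minutes with SDs of 15 to 30 minutes. They do not predict that such shifts will occur.

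**What to change.** State in Blinding and in Data collection and management that the 3-month actigraphy is scored masked to arm, and describe how:

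1. Someone who does not score, for example at LCTC, gives each recording and diary copy a random scoring code that carries no participant ID.
2. The Sleep Team scores against that code only and, where possible, no member scores a family they have phoned.
3. Scores are locked before the codes are linked back to participants.

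The cost is real but small. The Sleep Team now receives the devices and does the download, so files and copies of paper diaries need an extra transfer and recoding, and scoring starts a little later. Keeping callers and scorers apart needs a record of who phoned whom. No visit, outcome, sample size or participant burden changes. If the raw recordings and diaries are kept, masked scoring can still be done after collection.
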